# Protocol for a randomised, placebo-controlled, double-blinded clinical trial on the effect of oestrogen replacement on physical performance to muscle resistance exercise for older women with osteoarthritis of knee joint: the EPOK trial

**DOI:** 10.1186/s12877-023-03828-y

**Published:** 2023-02-18

**Keywords:** Oestrogen replacement therapy, Knee osteoarthritis, Muscle resistance exercise, Sarcopenia, Physical performance

## Abstract

**Background:**

Knee osteoarthritis (KOA) is highly prevalent in older women, and previous studies suggest the involvement of hormonal factors play a role in the pathogenesis of osteoarthritis. KOA causes musculoskeletal impairment, resulting in decreased physical activity, muscle mass, and strength, which leads to sarcopenia and further increases the burden on healthcare systems. Oestrogen replacement therapy (ERT) improves joint pain and muscle performance in early menopausal women. Muscle resistance exercise (MRE) is a non-pharmacological method that preserves the physical functions of patients with KOA. However, data on short-term oestrogen administration combined with MRE in postmenopausal women, especially in those aged > 65 years, are limited. Therefore, this study presents a protocol of a trial aimed to examine the synergistic effect of ERT and MRE on lower-limb physical performance in older women with KOA.

**Methods:**

We will conduct a double-blinded, randomised placebo-controlled trial in 80 Japanese women aged > 65 years living independently with knee pain. The participants will be randomly categorised into two groups: (1) 12-week MRE programme with transdermal oestrogen gel containing 0.54 mg oestradiol per push and (2) 12-week MRE programme with placebo gel. The primary outcome measured using the 30-s chair stand test, and secondary outcomes (body composition, lower-limb muscle strength, physical performance, self-reported measure of knee pain, and quality of life) will be measured at baseline, 3 months, and 12 months, and these outcomes will be analysed based on the intention-to-treat.

**Discussion:**

The EPOK trial is the first study to focus on the efficacy of ERT on MRE among women aged > 65 years with KOA. This trial will provide an effective MRE to prevent KOA-induced lower-limb muscle weakness, confirming the benefit of short-term oestrogen administration.

**Trial registration:**

Japan Registry of Clinical Trials: jRCTs061210062. Registered 17th December 2021, 
https://jrct.niph.go.jp/en-latest-detail/jRCTs061210062.

## Background

Japan is one of the countries with the highest ageing rate and is rapidly becoming a ‘super-aged’ society; by 2060, 40% of the population or more than 35 million people will be aged ≥ 65 years [1]. Healthy life expectancy is the average number of years an individual is expected to live in a state of self-assessed good or very good health based on current rate of mortality and prevalence of good or very good health [2]. The age difference between healthy and average life expectancies for women and men are 12.3 and 8.8 years, respectively, in Japan [3]. Reduced musculoskeletal function due to joint diseases decreases healthy life expectancy [4, 5]. In a large cohort study conducted in Japan [6], the prevalence rate of knee osteoarthritis was 80.7% and 51.6% among women and men aged ≥ 80 years, respectively, with women having a higher prevalence rate than men [7]. Japan has an estimated 44–48 million potential patients with knee and hip osteoarthritis [8]; the incidence rate is expected to further increase due to the rapidly ageing population.

Knee osteoarthritis (KOA) is the result of wear and tear and progressive loss of the articular cartilage [9]. It causes gradual deformation of the bones around the joint and the joint itself, resulting in joint pain and swelling. Impaired locomotion due to knee joint pain decreases physical activity. In addition, reduced activity leads to the loss of muscle mass and strength, decreased physical fitness, and weight gain, further exacerbating KOA pathology [10]. Decreased lower extremity muscle strength among patients with KOA [11] contributes to sarcopenia, which increases the risk of fall and fracture and the hospitalisation rate, leading to decreased activities of daily living (ADL) and ultimately to increased mortality. Preventive measures are needed before morbid conditions, such as sarcopenia and frailty, and development of and women-centric joint pain interventions are essential for further improvement in healthy life expectancies.

Non-surgical treatment guidelines by the Osteoarthritis Research Society International (OARSI) recommend muscle resistance (MREs), land-based, and water exercises, weight and self-management, and patient education as core treatments [12]. However, frequent interventions [13] and psychological [14] and social factors [15] may hinder sustained exercise motivation. Therefore, MREs need to be short and efficient, and a community system that provides reasons and support systems for continued exercising should be developed.

Oestrogen levels markedly decrease during menopause and are strongly associated with an increase in cardiovascular disease [16] and osteoporosis development [17]. Decreased blood oestrogen levels are also involved in KOA onset, with a significant sex difference and increased incidence in postmenopausal women [18, 19]. Skeletal muscle mass in women continues to gradually decline after peaking in their 20 s [20]; after menopause, the decline rapidly accelerates along with declining muscle strength [21–23]. Moreover, decreasing serum hormones levels, including growth hormone, dihydroepiandrosterone, and insulin-like growth factor-1, are related to a decrease in muscle mass during menopause [24]. Altogether, menopause can accelerate sarcopenia [25]. Oestrogen receptors are present in the articular cartilages [26], tendons, and muscles, and oestrogen helps in maintaining joint homeostasis [27]. Therefore, oestrogen plays a significant role in preventing the onset of osteoarthritis [28, 29] and helps in the development and regeneration of skeletal muscle [30] after menopause. In the Women’s Health Initiative randomised controlled trial (RCT), oestrogen replacement therapy (ERT) in postmenopausal women moderately reduced knee pain frequency and attenuation [31].

The effects of hormone replacement therapy (HRT) on muscle mass and strength in postmenopausal women remain controversial. A recent meta-analysis based on 12 RCTs concluded that HRT without training had no beneficial or detrimental effect on muscle mass, but a significant bias existed in half of the clinical trials [32]. However, a recent clinical trial showed that transdermal oestrogen application with MRE increased the skeletal muscle cross-sectional area compared with that noted with a placebo [33]. A meta-analysis published in 2009 reported that HRT increased the muscle strength in both observational and interventional trials [34]. However, a recent meta-analysis based on nine RCTs of 2,476 postmenopausal women concluded that using HRT without training was not associated with improved muscle strength [35]. Only few studies have investigated the effect of MRE combined with HRT in postmenopausal women [33, 36, 37]. To the best of our knowledge, the synergistic effect of HRT and MRE on muscle strength has not been previously elucidated. Moreover, previous studies [36, 37] on the effect of HRT on skeletal muscles have focused on healthy postmenopausal women in their early 50 s, with only few studies on women in their 70 s and 80 s when muscle weakness begins impacting their lives and few interventional studies on women with joint diseases have been reported.

## Methods/design

### Aim

We designed the EPOK trial to determine the synergistic effect of ERT and MRE on physical performance in the lower limbs of older women with KOA. We hypothesise that oestrogen administration and a muscle resistance exercise programme (MREP) will increase the 30-s chair stand test (CS-30) score, lower extremity strength, and subjective well-being of the participants. If the synergistic effects of oestrogen and the MREP on lower-limb physical function are confirmed, we can administer short-term oestrogen with MREP for KOA and other conditions, such as sarcopenia, wherein physical performance and lower-limb muscle strength are declined.

This protocol complies with the Standard Protocol Items: Recommendations for Interventional Trials (SPIRIT) 2013 guideline [38] for clinical trials and the Consolidated Standards of Reporting Trials 2010 statement [39].

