### Study design

The EPOK trial is a two-arm exploratory double-blinded RCT with a 12-week intervention period, and the outcomes will be measured at baseline, 3 months, and 12 months. Figure 1 outlines the RCT phases. Eighty participants will be identified and randomly categorised into two groups: (1) MREP with transdermal oestrogen gel and (2) MREP with placebo gel. Eligibility will be assessed during screening. The Okayama University Hospital and Ochiai Hospital will conduct this trial. We have organised the EPOK trial team, including the Maniwa City Community General Support Center, which will assist with recruitment via telephone, mail, local newspapers, and public health seminars. The non-profit organisation (NPO) of the agri-garden project will assist with MREP coaching. Figure 2 outlines the trial design schedule following the SPIRIT guidelines [38].

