### Statistical analysis

The MREP participants will be assigned to either the oestrogen or placebo group. Data will be aggregated for the assigned analysis participants at baseline, 3 months, and 12 months after the intervention. The target population will be the full analysis set, defined as all the randomised participants who have started their trial treatments.

The statistical analysis will be based on the intention-to-treat and per-protocol principles. The participants’ demographic background and baseline characteristics will be described as appropriate, with data presented as mean and standard deviation for continuous variables that appear to be approximately normally distributed, as medians and interquartile ranges for other continuous variables, and as counts and percentages for categorical variables. Linear regression analysis will be performed for a statistical comparison of the primary and secondary outcomes between the oestrogen and placebo groups. The relationship between the intervention and endpoints will be calculated as a regression coefficient with a 95% confidence interval. The covariate distribution is expected to be consistent across the groups due to randomisation. Therefore, only the presence or absence of intervention will be used as an explanatory variable for the linear regression analysis. However, the variable distribution will be biased by chance due to allocation; thus, the variable is added to the explanatory variables and an adjustment is made. We will adopt a complete case analysis as the primary analysis if the proportions of missing data are < 5%. Multiple imputations will be conducted if imputation of > 5% is required for the amount of missing data for an outcome, and the method will be reported.

The statistician, who is blinded to the allocation, will perform the analysis at the Department of Obstetrics and Gynaecology, Graduate School of Medicine, Dentistry, and Pharmaceutical Sciences, Okayama University. The validity of the analysis will be verified by the Centre for Innovative Clinical Medicine and Department of Epidemiology of the Okayama University as a third-party institution.

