### Muscle resistance exercise programme

The MREP will implement the same content for both the intervention groups, with one training session per week to be held in a group and two sessions per week at home. Twelve group sessions will be held at the community centre in each district where an instructor will be present to ensure training quality and provide guidance. The Maniwa Agri-garden-project NPO provides the MREP instructors with a group session. The exercise instructors will have a 2-h lesson provided by an experienced physiotherapist from the Okayama University Hospital and will receive certified coaching insurance from the CI. Each group session will last 90 min, including a 15-min break.

The group MREP session will comprise an evidence-based programme designed by a physiotherapist at the Okayama University Hospital. The MREP is a multi-component exercise programme with a beneficial effect on the physical functions of patients with KOA, consistent with the current standard of care and clinical practice guidelines [51–53]. It includes a dynamic warm-up with range of motion stretches (approximately 10 min), MRE (approximately 25 min), balance training [54] (approximately 10 min), cool-down with stretches (approximately 5 min), and a coordinated dual-task section [55] (approximately 25 min). The MRE was designed based on the OARSI guideline [56, 57], a structured land-based exercise programme focusing on the four major lower-limb muscle groups (quadriceps, calf muscle, hamstrings, and gluteal muscles), and abdominal and back muscles in patients with KOA. The MRE section consists of chair-based and standing exercises, including knee extension, knee lift exercises from sitting and standing positions, heel raise, squats, and chair standing exercises. Each movement will take 6–8 s, with the participants counting the seconds out loud. Each exercise will comprise two sets of 8–10 repetitions with gradually increasing muscle load [54] and number of repetitions based on the participant's perceived exertion. Weeks 1–4 will have no weight load, and 1.0 kg ankle weights will be used to increase the muscle load from week 5. The exercise instructor will supervise the participants by providing verbal feedback to ensure that the target muscle groups obtain sufficient tension.

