## Discussion

Musculoskeletal disorders, including osteoarthritis [11] and osteoporosis [17], are more common in postmenopausal women, and the decline in muscle strength and physical function due to these effects can lead to a ‘negative spiral’ of falls, fractures, and sarcopenia development [7]. Therefore, preventive measures are required for these women. The EPOK trial is the first study to focus on the synergistic effect of oestrogen and MRE on KOA in women older than 65 years. If this trial's successful implementation proves the effectiveness of ERT in improving physical function in older women, it could lead to effective short-term interventions during MRE for joint diseases and muscle weakness, such as sarcopenia.

One of the strengths of this EPOK trial is that it is a placebo-controlled, double-blind RCT that adequately measures oestrogen effects on the musculoskeletal system using primary and secondary outcomes. However, we will not perform muscle or cartilage biopsy to investigate the oestrogen effect using immunohistochemical methods because of the high invasiveness and burden of frequent hospital visits for the participants.

In this trial, two interventions will be implemented to observe their effects on the musculoskeletal system, particularly in the lower extremities. Based on previous evidence, the MREP will be a multi-component programme. The weekly coaching will ensure exercise quality, and home training will allow the participants to monitor the amount of exercise done using photo handouts and filling-in exercise assessments. Transdermal oestrogen administration reduces the side effects on hepatic metabolism such as thrombosis and increased triglyceride levels. The gel formulations will be simple to administer, and the bottles will be designed to ensure consistent and accurate dosage. The 12-week intervention period will be adequate to ensure exercise continuity and measure the effects of oestrogen administration. The interventions are practical due to close collaboration with municipal healthcare services, including local governments and NPOs. Thus, these two interventions can be easily and accurately implemented.

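### The aim is worded as oestrogen–exercise synergy, but with exercise in both arms the trial can estimate only what oestrogen adds to exercise

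*Protocol article*

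**What the plan says.** **Stated question.** The Aim section gives the purpose as "to determine the synergistic effect of ERT and MRE on physical performance in the lower limbs of older women with KOA". The abstract's background states the same purpose, and the Discussion calls the trial "the first study to focus on the synergistic effect of oestrogen and MRE on KOA in women older than 65 years".

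**Planned conclusion.** The Aim section makes it conditional on synergy: "If the synergistic effects of oestrogen and the MREP on lower-limb physical function are confirmed, we can administer short-term oestrogen with MREP", for knee osteoarthritis and for other conditions such as sarcopenia.

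**Arms.** Study design lists two: "1) MREP with transdermal oestrogen gel and (2) MREP with placebo gel". The section on the exercise programme adds: "The MREP will implement the same content for both the intervention groups". No arm without exercise is described anywhere.

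**Analysis.** Statistical analysis says: "Linear regression analysis will be performed for a statistical comparison of the primary and secondary outcomes between the oestrogen and placebo groups". The only explanatory variable is the intervention indicator, apart from adjustment for variables that turn out unbalanced by chance.

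**Sample size.** Sample size and power analysis takes an oestrogen gain of 13% on a mean chair-stand (CS-30) score of 9.2. It places this on top of 2.68 repetitions attributed to the exercise programme alone, a figure from an outside source.

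**The concern.** In statistical terms, two treatments are synergistic when their joint effect exceeds the sum of their separate effects. To show this, one needs the effect of oestrogen in women who exercise and the effect of oestrogen in women who do not. The trial randomises oestrogen only among women who all exercise, so the second effect has no data.

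What is at stake is the claim that may be made afterwards. A clear oestrogen–placebo difference would show that oestrogen adds something for exercising women. It would not show that oestrogen works better because they exercise. Yet the Aim section speaks of synergy being confirmed and builds the proposed use on it. A reader of the eventual report could take an add-on result as evidence of interaction that was never tested.

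**Working it through.** **1. Reproduce the plan's own figure.** Inputs from Sample size and power analysis: effect size d = 0.6, one-sided alpha 5%, power 80%, dropout about 10%.

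- Normal approximation: n = 2 × ((1.645 + 0.842) / 0.6)² = 34.4, so 35 per group.
- t-test solution: 35.04, so 36 per group, with power 0.809.
- Dropout: 36 / 0.90 = 40 per group, 80 in total.

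The stated 36 and 40 reproduce. They size the difference between oestrogen and placebo among exercising women, and nothing else.

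**2. The assumed add-on gain.** 13% of 9.2 = 1.196, about 1.2 repetitions. The protocol's sentence on this is loosely worded (it speaks of 1.2 times the improvement). I read it as 1.2 repetitions because that is what 13% of 9.2 gives.

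**3. What synergy requires.** Write the four possible mean gains as oestrogen + exercise, exercise only, oestrogen only, and neither. Then

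synergy = (oestrogen + exercise − exercise only) − (oestrogen only − neither).

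The two arms supply the first bracket. Neither term of the second bracket is observed. One of the two contrasts is available, and the interaction is their difference.

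**4. What an add-on gain of 1.2 is compatible with.** Take the plan's 2.68 for exercise alone and set the gain with neither treatment to 0. The values for oestrogen alone are illustrative assumptions.

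| Oestrogen alone | Interaction | Exercise + placebo | Exercise + oestrogen | Two-arm difference | Reading |
|---|---|---|---|---|---|
| 1.2 | 0 | 2.68 | 3.88 | 1.2 | additive |
| 0.6 | 0.6 | 2.68 | 3.88 | 1.2 | partly synergistic |
| 0 | 1.2 | 2.68 | 3.88 | 1.2 | wholly synergistic |
| 2.0 | −0.8 | 2.68 | 3.88 | 1.2 | antagonistic |

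Both observable arm means are identical in all four rows. Recruiting more women would estimate 2.68 and 3.88 more precisely and still leave the four rows indistinguishable. The problem is identification, not power.

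**The case against.** **The word may only mean combined.** The hypothesis sentence in the Aim predicts gains under oestrogen plus exercise and states no interaction. The abstract's discussion speaks of the efficacy of oestrogen on exercise, and the Discussion of measuring oestrogen effects. These phrases fit an add-on question. But the Background separates the two ideas: it reports a few studies of exercise combined with hormone therapy and then says their synergistic effect on muscle strength is still unknown. Synergy is therefore presented as a gap beyond combined use, and the loose reading does not hold.

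**Oestrogen without exercise may do nothing.** If so, the second bracket would be zero and the add-on effect would equal the interaction. The Background does cite two meta-analyses with null results for hormone therapy without training. It also calls the evidence controversial, notes significant bias in half the trials of one of them, and cites a third meta-analysis that found increased strength. The sample size section itself uses a general oestrogen strength gain of 5% to 17%. A zero effect is nowhere stated as an assumption, so this softens the point without answering it.

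**The decision does not need synergy.** Whether to add oestrogen to exercise depends on the add-on effect, which the trial does randomise. This stands, and it is why the remedy is confined to wording.

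**The trial is labelled exploratory.** That can excuse imprecision. It cannot supply a contrast for which there are no data.

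**Stronger readings to avoid.** A reader might infer that the trial is invalid, or too small for its primary comparison. The documents do not support that: arms, analysis and sample size all target the same add-on effect. A reader might also infer that the protocol declares any positive result to be proof of synergy. It gives no such rule; the Aim sentence is conditional. Nor does the protocol claim that change within the placebo arm measures the exercise effect.

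**Conclusion.** The point holds as a mismatch between the stated question and the design. The abstract, the Aim and the Discussion name synergy, and the Aim makes its planned conclusion depend on it. The design identifies one of the two contrasts that synergy needs, so an add-on gain of about 1.2 repetitions says nothing about the sign or size of the interaction, at any sample size.

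This rests on the usual meaning of synergy as an interaction on the scale of the chair-stand count, and on there being no non-exercising arm. It does not depend on the illustrative values chosen for oestrogen alone. The oestrogen–placebo comparison in exercising women, with 36 (target 40) per group, is a coherent plan for the narrower question.

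**What to change.** - In the abstract's background, the Aim and the Discussion, replace the synergy wording with: *additional effect of transdermal oestrogen over placebo in women undertaking the MREP*.
- In the Aim, reword the sentence that begins "If the synergistic effects of oestrogen and the MREP on lower-limb physical function are confirmed" so that its condition is the add-on effect.
- Add one sentence saying that synergy, meaning an oestrogen-by-exercise interaction, cannot be assessed because no participants are randomised to go without the exercise programme.

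The cost is a narrower headline claim. Arms, sample size and analysis stay as they are.

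Keeping synergy as the question would require a different trial. As an illustration only, assume a 2×2 design and an interaction of d = 0.6, with one-sided 5% alpha and 80% power. The need is 4 × ((1.645 + 0.842) / 0.6)² = 68.7, so 69 per cell and 276 in total before dropout. At an assumed d = 0.3 it is 275 per cell, or 1,100 in total. The rewording avoids this.
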